## Methods/design

The study is a two-arm randomized controlled trial design conducted at The University of Queensland School of Human Movement and Nutrition Sciences. All primary and secondary outcomes will be measured at baseline, week 8, 12, and 20. A total of 116 men with prostate cancer treated with ADT (>3 months) will be randomized to either a 20-week nutrition therapy with 8 weeks of high intensity exercise (performed from weeks 12 to 20) or a control group of usual care. A person independent to the study will conceal participant allocation, after baseline testing using a random number generator into either group, with equal probability. The study will be guided by the CONSORT statement [44] (Fig. 1).

**Fig. 1 Fig1:**
[figure not shown]
CONSORT diagram and schematic representation of the study. Legend: Wk = week, HIIT = high intensity interval training

### Participant eligibility

To be eligible to participate in this study, men must meet the following inclusion criteria: (a) aged ≥18 years, (b) non-smoker, or have quit smoking for ≥3 months, (c) a diagnosis of prostate cancer, and have been undertaking ADT for ≥3 months, (d) body mass index of 18.5-34.9 kg/m^2^ (i.e. normal weight, overweight or obese class I). Exclusion criteria include: (a) taking any supplements other than a single multivitamin, unless stated for medical purposes, (b) have any musculoskeletal, neurological, respiratory, metabolic or cardiovascular conditions that may prevent safe completion of the exercise demands of the study, as determined by a Urologist, (c) current infection, (d) bone metastases, (e) currently undertaking high intensity exercise i.e. ≥90% heart rate max (HR_max_) or ≥7 rating of perceived exertion (RPE; Borg’s rating of perceived exertion scale, category scale 0-10).

### Recruitment and informed consent

Participants will be recruited from the Mater Adults Hospital, Brisbane, Australia; The University of Queensland, Australia; and the Cancer Council Queensland, Australia. Participants will also be recruited by way of media releases, presentations and advertisements in newsletters, newspapers, and noticeboards at The University of Queensland, Cancer Council Queensland, and the Prostate Cancer Foundation of Australia support groups. All participants will be complete a brief telephone screening questionnaire to verify eligibility. Eligible participants will be asked to seek guidance from their Urologist regarding participation in the study, and sign the consent form prior to participating in the study. Approval of the trial protocol was obtained from the Mater Research Ethics Committee (HREC/15/MHS/38) and The University of Queensland Human Research Ethics Committee (2015001245) prior to recruitment.

### Randomisation

After baseline testing, participants will be randomly allocated to either the nutrition therapy with high intensity exercise or the standard care group using a 1:1 ratio. The randomisation process will be conducted by a computerized system using a random number generator, with equal probability, by a person external to the study.

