### Sample Size Calculation

Sample size calculations were complete using Vanderbilt Power and Sample Size software (Vanderbilt University, TN). Combined diet and exercise interventions with CRF as an outcome are relatively limited. A diet and exercise intervention in men treated with ADT showed prostate cancer-specific CRF (as measured by FACT-F) scores improved by 3.7 – 14.2 (CI, 95%; adjusted mean 8.9 points) in the intervention group compared to the control group [20]. Assuming FACT-F scores for this group were normally distributed with a SD of 8.9, a true difference between the experimental and control arms of 5.2, and a power of 0.8, we would need 47 experimental and control participants to be able to reject the null hypothesis. The type 1 error probability associated with this test of the null hypothesis is 0.05. With an anticipated 20% attrition rate based on previous research from our laboratory, we would need 58 experimental and control group participants to be able to reject the null hypothesis.

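### The allocation as described may leave baseline fatigue to chance, and the listed analyses do not commit to adjusting for it; the primary FACT-F comparison should carry baseline FACT-F as a covariate

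*Protocol article*

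**What the plan says.** Two sections of the protocol article describe allocation. Methods/design has an independent person allocate men after baseline testing "using a random number generator into either group, with equal probability". The Randomisation section gives the allocation as "using a 1:1 ratio" and then describes a computerised process "using a random number generator, with equal probability, by a person external to the study". Neither section names blocks, strata or minimisation, and neither uses the term simple randomisation.

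The planned total is 116 ("A total of 116 men with prostate cancer treated with ADT"). The Sample Size Calculation section assumes FACT-F scores "normally distributed with a SD of 8.9" and "a true difference between the experimental and control arms of 5.2, and a power of 0.8", from which "we would need 47 experimental and control participants to be able to reject the null hypothesis". After 20% attrition, "we would need 58 experimental and control group participants".

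Table 1 lists FACT-F first among the primary outcomes, measured at baseline and at weeks 8, 12 and 20. The Statistical Analysis section offers a menu: descriptive statistics, t tests, correlation, regression, and two-way repeated measures ANOVA or a non-parametric counterpart. Baseline is one of the time points. The section does not say which method tests the primary between-group comparison, or whether baseline FACT-F enters it as a covariate.

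**The concern.** FACT-F at baseline is known before each man is allocated and is likely to predict his later score. If the list is unrestricted, nothing in the design balances it. If the primary comparison is then a t test on follow-up scores, a chance gap at baseline carries through to the result in part. If it is a change-score or group-by-time comparison, the gap is over-corrected whenever the correlation between baseline and follow-up is below 1. In both cases precision that the trial has already paid for is lost.

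The outcome is self-reported, and men will know whether they received dietetic consultations and supervised cycling. A visible baseline difference in fatigue would therefore make the result easier to dispute, even though the test remains valid.

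**Working it through.** **Inputs.** From the Sample Size Calculation section: difference 5.2, SD 8.9, power 0.80, type 1 error 0.05 (taken as two-sided, which reproduces the plan's figure), attrition 20%, 58 per arm. Assumed, because the article does not give them: baseline SD 8.9, equal SDs at baseline and follow-up, and a baseline-to-follow-up correlation ρ of 0.4 to 0.7.

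**1. The plan's figure.** n per arm = 2 × (8.9 × (1.960 + 0.842) / 5.2)² = 46.0 by the normal approximation. The t-based solution is 46.96, so 47: reproduced. For attrition, 47/0.8 = 58.75 and 46/0.8 = 57.5, so the stated 58 is right to within rounding. With 58 × 0.8 = 46.4 evaluable per arm, the t-test power is 79.5%.

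**2. Arm sizes, if each man is drawn independently with probability 0.5.** From Binomial(116, 0.5):

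- exactly 58:58 in 7.4% of trials;
- 50:66 or worse in 16.3%, and 48:68 or worse in 7.7%;
- 95% range for one arm: 47 to 69.

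Power by t test after 20% attrition:

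| Split | Power |
|---|---|
| 58:58 | 79.5% |
| 53:63 | 79.2% |
| 50:66 | 78.7% |
| 48:68 | 78.3% |
| 47:69 | 78.1% |

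Averaged over all splits, power is 79.2%. The loss is 0.3 points on average and about 1.2 points at 48:68.

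**3. Chance difference in baseline FACT-F.** SE = 8.9 × √(2/58) = 1.65, so the 95% range is ±1.96 × 1.65 = ±3.2 points. The probability of a gap above 2.6 points (half of 5.2) is 11.6%. Unequal arms hardly change this: the SE is 1.68 at 47:69.

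**4. What a 2.6-point gap does to each analysis.** In expectation it shifts an unadjusted follow-up comparison by ρ × 2.6 = 1.04 to 1.82 points. It shifts a change-score comparison by (1 − ρ) × 2.6 = 1.56 to 0.78 points in the opposite direction. Both ranges are 15% to 35% of the 5.2-point target. A model with baseline as a covariate removes the shift if the relation is linear.

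**5. Power at 46.4 per arm for a difference of 5.2.** The effective SD is 8.9 for follow-up scores, 8.9 × √(2(1 − ρ)) for change scores, and 8.9 × √(1 − ρ²) with baseline as a covariate.

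| ρ | Follow-up only | Change score | Baseline as covariate |
|---|---|---|---|
| 0.4 | 79.5% (SD 8.90) | 72.0% (SD 9.75) | 85.9% (SD 8.16) |
| 0.5 | 79.5% (SD 8.90) | 79.5% (SD 8.90) | 89.5% (SD 7.71) |
| 0.7 | 79.5% (SD 8.90) | 94.9% (SD 6.89) | 97.4% (SD 6.36) |

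The covariate model has the highest power in every row. The baseline-to-week contrast within a group-by-time ANOVA corresponds to the change-score column.

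**The case against.** The strongest case against the point has four parts.

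*The list may not be simple.* A reader might infer that the protocol states simple randomisation and so fails to secure 58 per arm. It does not state this. A blocked list also gives each man an equal chance of either arm, and the Randomisation section specifies a 1:1 ratio. Block and stratum details are commonly left to a full protocol that is not shown. This part stands: unrestricted allocation is the natural reading, but it remains an inference.

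*Arm-size imbalance is immaterial.* A reader might infer that unequal arms threaten the power. The table in step 2 shows that they do not. This part stands in full.

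*Chance imbalance is not bias.* Under valid randomisation the type 1 error already allows for it. This also stands; the cost is precision and ease of interpretation.

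*The plan can already adjust.* A reader might infer that nothing in the analysis could repair a baseline gap. Regression is listed, and a repeated measures ANOVA with baseline as a time level does use baseline, so that inference goes too far. Exact covariates are also often left to a statistical analysis plan. What remains is that the section puts methods of quite different precision side by side without choosing among them, and the choice moves power by several points or more.

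Restricting the list is a trade-off as well. In a single-site trial whose participants cannot be masked, unrestricted allocation is the hardest to predict, and blocks within strata give up some of that protection.

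**Conclusion.** The point holds as a minor one about precision. The allocation text most naturally leaves baseline FACT-F to chance, with a standard error of about 1.65 points between arms, and the listed analyses do not commit to adjusting for it. Committing to baseline as a covariate takes power at the planned size from 79.5% to about 86% to 97% relative to unadjusted follow-up scores. Relative to change scores the gain is about 14 points at ρ = 0.4 and 2 to 3 points at ρ = 0.7.

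These figures rest on the assumed correlation and on 8.9 being the SD of scores at both baseline and follow-up. If 8.9 were instead the SD of change, the covariate model would still have a residual variance of (1 + ρ)/2, or 0.70 to 0.85, of the change-score variance, so the direction does not depend on that reading. The documents do not support a claim of bias, of an invalid randomisation, or of a material loss of power from unequal arms.

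**What to change.** In the Statistical Analysis section, or in the analysis plan before the data are examined by arm, specify the primary between-group FACT-F comparison at weeks 12 and 20, the time points of the two aims. Use a model with baseline FACT-F as a covariate: ANCOVA at each week, or a mixed model for repeated measures over the follow-up visits with baseline as a covariate. This replaces an unadjusted t test or a group-by-time ANOVA with baseline as a time level.

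The cost is a few sentences and one degree of freedom. Baseline FACT-F is already collected, and neither the sample size nor the visit schedule changes.

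One sentence saying whether the list is simple or restricted would also help. A stratified block list is optional. If it is chosen, block sizes should vary and stay concealed, because participants cannot be masked, and the stratum should enter the model.

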### Measurements

All measurements for primary and secondary outcomes will take place at baseline, week 8, week 12, and week 20 (see Table 1). A familiarization trial including the functional capacity and peak aerobic power (V̇O_2peak_) tests will take place at least 7 days prior to baseline testing. Participants will be asked to refrain from vigorous exercise, caffeine, alcohol, food and beverages (except for water) for 12 h before all testing sessions.

**Table 1 Tab1:** Data collection schedule

Assessments	Time (weeks)				
	Baseline^a^		Week 8	Week 12	Week 20
Screening					
Participant eligibility	✓	Randomization			
Adult Pre-exercise Screening System	✓				
Medical history form and medications	✓				
Primary outcomes					
Function Assessment of Cancer Therapy-Fatigue	✓	Randomization	✓	✓	✓
European Organization of Research and Treatment of Cancer QLQ-C30*	✓		✓	✓	✓
European Organization of Research and Treatment of Cancer QLQ-PR25^□^	✓		✓	✓	✓
The Medical Outcomes Study 36-Item Short-Form 36	✓		✓	✓	✓
Second Outcomes					
Anthropometric physique traits	✓	Randomization	✓	✓	✓
Body composition^b^	✓		✓	✓	✓
Isometric strength	✓		✓	✓	✓
Chest and leg one repetition maximum test	✓		✓	✓	✓
Sit to stand test	✓		✓	✓	✓
Six-meter walk test	✓		✓	✓	✓
400-meter walk test	✓		✓	✓	✓
Cardiorespiratory fitness^c^	✓		✓	✓	✓
Blood collection	✓		✓	✓	✓
Wollongong Dietary Inventory	✓		✓	✓	✓
24-h diet recall^d^	✓		✓	✓	✓
Depression Anxiety Stress Scale	✓		✓	✓	✓
Insomnia Severity Index	✓		✓	✓	✓
Physical Activity Enjoyment Scale	✓		✓	✓	✓
Godin Leisure-Time Physical Activity Questionnaire	✓		✓	✓	✓
Accelerometer^e,f^	✓		✓	✓	✓

^a^Nutrition and exercise intervention commences Week 0 after randomisation

^b^Dual energy X-ray absorptiometry

^c^V̇O_2peak_ test

^d^Conducted every 2 weeks

^e^Actigraph GT3X+

^f^to be worn for 7 consecutive days

*Cancer quality of life questionnaire for people with cancer

^□^Cancer quality of life questionnaire for people with prostate cancer

### Primary outcomes

#### Fatigue

Fatigue will be measured using The Functional Assessment of Cancer Therapy: Fatigue (FACT-F) questionnaire, which reports weekly fatigue on a scale of 0–52, with higher values indicating less fatigue [45]. The FACT-F has shown good reliability and validity (Cronbach’s α: 0.93-0.94) for predicting clinically significant treatment outcomes of CRF [46].

#### Cancer-specific quality of life

The European Organization for Research and Treatment of Cancer (EORTC) QLQ-C30 is a 30 item cancer-specific instrument including the following domains; physical, role, emotional, social, and cognitive, global quality of life, fatigue, pain, and emesis. The EORTC QLQ-C30 has shown a high reliability (Cronbach’s α; 0.63-.80) in cancer patients [47].

#### Prostate cancer-specific quality of life

The EORTC QLQ–PR25 is a 25 question prostate cancer-specific instrument including domains; urinary, bowel, use of incontinence aids, treatment-related symptoms, sexual activity and sexual function [48]. The EORTC QLQ – PR25 questionnaire has shown good internal reliability (Cronbach’s α; 0.70-0.86) for prostate specific treatment-related side effects [49].

#### General health and well-being

The Medical Outcomes Study 36-Item Short-Form 36 Health Survey (SF-36) is scored by eight scales encompassing physical and mental measures [50]. The SF-36 questionnaire has widely been used to measure general health and well-being, with good construct validity (Cronbach’s α; > 0.85) in cancer patients [51].

### Secondary outcomes

#### Physique traits and body composition

Height, body mass, and waist circumferences will be measured according to the International Society for the Advancement of Kinathropometry (ISAK) procedures [52].

Body composition (fat mass, lean mass, body fat percentage and bone mineral density) will be assessed using dual energy X-ray absorptiometry (DXA; Hologic Discovery A, Waltham, MA, USA).

#### Muscular Strength and Power

Isometric strength of dominate and non-dominate handgrip will be assessed using a spring-loaded grip dynamometer (TTM, Tokyo, Japan) to estimate physical performance [53], and muscular strength [54]. Participants will perform the test three times on each hand with the best result used for analysis. Muscular strength of the chest and legs will be measured using the one repetition maximum (1RM) chest and leg press methods, respectively [55]. The sit to stand test will be used to assess functional leg power [12]. Participants will perform the test three times with the best result used for analysis.

#### Exercise capacity and cardiorespiratory fitness

The six-meter walk test will involve participants walking a marked 10-m distance as quickly as safely possible, with performance timed over the middle 6-m distance to minimize the influence of acceleration and deceleration [12]. The 400-m walk test will be used to estimate exercise capacity [12]; participants will be required to walk 10 laps out and back over a 20-m course (400 m total) as fast as safely possible.

Cardiorespiratory fitness will be assessed using a V̇O_2peak_ test. The test will involve a modified ramp protocol described by Wasserman et al [56] on a cycle ergometer. Participants will begin with 3 min of rest for respiratory normalization, followed by 4 min of warm-up at a resistance of 50 Watt. The electrical resistance provided by the cycle ergometer increases incrementally by 20-30 W.min^-1^. Participants will cycle at a cadence between 60 and 70 revolutions per minute throughout the test. Heart rate will be continuously recorded throughout the exercise using a heart rate monitor (Polar FT1; Polar, Kempele, Finland) and blood pressure (Durashock Sphygmomanometer; Welch Allyn, New York, USA) will be recorded every 2 min throughout the test. At the conclusion of each minute participants will indicate their rating of perceived exertion (RPE) on the Borg 6-20 scale [57]. The test will be terminated when the participant reaches volitional fatigue or at the discretion of the researchers with consideration for exercise testing termination criteria as outlined by the American Association of Cardiovascular and Pulmonary Rehabilitation [58]. The gas analyzers and ventilometer will be calibrated prior to and verified after each test. Sampled expired air will be measured every 15 s using a turbine ventilometer (Morgan, Model 096, Kent, England). The ramp V̇O_2peak_ protocol has good validity in comparison to the standard Bruce protocol [59]. V̇O_2peak_ will be recorded as the highest V̇O_2_ reading averaged over two consecutive readings.

#### Blood collection and analysis

A trained phlebotomist will extract, treat and subsequently store the blood at approximately -80°C until later analysis. Analysis of blood samples through commercial ELISA kits (Thermo Fisher Scientific Australia Pty Ltd., Victoria, Australia; Randox Laboratories Ltd., West Virginia, USA; R&D Systems Inc., Minneapolis, USA) will be used for PSA, IGF-1, IGF-2, IGFBP3, IL-6, IL-8, Hepcidin, total cholesterol, and triglycerides analysis.

#### Dietary intake

Participants will complete the Wollongong Dietary Inventory [60] (a comprehensive dietary history of intake over the past month) with cross-checking quantification from an Accredited Practising Dietitian. Narrative approaches to diet histories have been shown to provide good reproducibility and reliability compared to food records [61]. Food models and pictures of food portions (Great Ideas in Nutrition, Coolangatta, Australia) will be utilized to improve the accuracy of food intake estimates [62].

### Other measures

#### Psychosocial: Depression Anxiety Stress Scale (DASS)

The DASS is a 42-item self-report instrument design to measure the three related negative emotional states of depression, anxiety, and stress [63], and has been validated for measuring emotional states of depression (Cronbach’s α: 0.94), anxiety (Cronbach’s α: 0.88) and stress (Cronbach’s α: 0.93) in clinical populations [64].

#### Insomnia Severity Index (ISI)

The ISI questions relate to subjective qualities of the respondents sleep, including satisfaction with sleep patterns, the degree to which insomnia interferes with daily functioning, and how the respondent feels their insomnia is noticeable to others [65]. The ISI has shown excellent internal consistency (Cronbach’s α: 0.90) for detecting symptoms of insomnia.

#### Physical activity enjoyment scale (PACES)

The physical activity enjoyment scale (PACES) will be used to assess participant enjoyment of the high intensity interval exercise PACES consists of 17 subscales that each relate to an aspect of enjoyment; along a 7-point continuum for each subscale, participants are asked to provide a rating to reflect their agreement with one of two bi-polar statements (e.g. ‘I enjoy it’ – ‘I hate it’) [66]. The PACES questionnaire has shown high internal consistency (Cronbach’s α: 0.90) in measures of exercise enjoyment [67].

#### Godin leisure-time physical activity questionnaire

The Godin leisure-time physical activity questionnaire requires participants to recall during a typical 7-day week the frequency and duration of exercise completed at three separate intensities: mild, moderate, and strenuous intensity [68]. The Godin leisure-time physical activity questionnaire has shown high agreement and validation (agreement: 70.8%) with minutes spent physically active, in comparison to an accelerometer in breast cancer survivors [69].

#### Accelerometer

Participants will be asked to maintain their current level of physical activity outside of the testing sessions for the duration of the study. Physical activity will be objectively assessed using the Actigraph GT3X+ accelerometer (Actigraph, Pensacola, Florida), a small, waist-worn, non-invasive device. Few studies have been published on the validity of the GT3X+ version of the Actigraph accelerometer specifically, however previous versions of the Actigraph accelerometer (CSA and GT1M) have demonstrated waist-worn validity in treadmill walking and running compared with indirect calorimetry (*r* = 0.56, *p* < 0.001 and *r* = 0.53, *p* < 0.05, respectively) in adults [70, 71].

### Interventions

#### Nutrition therapy with high intensity exercise

Detailed diet histories will be conducted at baseline week 8, 12 and 20 using the Wollongong Dietary Inventory [60], and 24 h diet recalls every two weeks during the intervention. Each consult will take approximately 30-45 min and involves an Accredited Practising Dietitian asking detailed questions about the foods consumed and the amount and frequency of consumption. The 20-week diet emphasizes a total energy intake decrement using the Harris-Benedict predicted energy requirements [72]; with a dietary composition of 45-65% carbohydrate, 20-35% fat, saturated fat <10% total energy intake, and 15-25% protein sources. Dietary advice will be tailored according to current body composition classification as ‘normal, overweight or obese stage I’ (see Fig. 2). A dietary energy reduction of 2000-4000 kJ/day will be emphasized at baseline consultation if body composition and diet intake are classified average or poor according to Fig. 2: Nutrition therapy schematic representation. The diet intervention will encompass a Mediterranean-style diet containing cruciferous vegetables (broccoli, bok choy, cauliflower) [73], tomato and tomato-paste containing products (lycopene) [74, 75], fruits, calcium and vitamin D containing foods, polyunsaturated, monounsaturated, omega 3 and 6 fatty acids (<10–15% total energy intake) [76], and a reduced consumption of red meat (<2 a week) [77, 78]; as seen in Table 2: Nutrition recommendations. Each individual nutritional consultation, will aim to make gradual changes to the participants’ diets to best achieve a modified Mediterranean-style dietary pattern. Standard dietetics practice will be used to assess and providing guidance on managing the nutritional impact symptoms from treatment (including broader intolerances/allergies).

